#### 5.10.4 Blood sampling volumes

The maximum planned volumes of blood sampled per subject are

|                                 | Screening visit | Visit III
(Day 2)                                                                   | Visit IX
(Day 10)                                                                   | AV1, AV2, AV3 on
Day 30, 90, 180 after
boost shot |
|---------------------------------|-----------------|----------------------------------------------------------------------------------------|----------------------------------------------------------------------------------------|---------------------------------------------------------|
| Visit window                    | -7 to -3        | 0                                                                                      | $\pm 1$ day                                                                            | $\pm 3$ day                                             |
| Immunogenicity blood
samples | 9 ml EDTA       |                                                                                        | 9 ml EDTA
up to 45 ml EDTA/heparin                                                  | 9 ml EDTA
up to 45 ml EDTA/heparin                   |
| Other lab values                |                 | Clinical chemistry
and blood count
3 ml citrate
5.5 ml heparin
2.7 ml EDTA | Clinical chemistry and
blood count
3 ml citrate
5.5 ml heparin
2.7 ml EDTA |                                                         |

#### 5.11 Third dose off vaccination

Participants that are eligible to a third vaccine dose as described above due to a lack of neutralizing antibody response on day 90 might be enrolled for the third vaccination between day 110 and 180. All other participants that have been followed till day 180 might be enrolled for a third vaccination between day 200 and 260.

#### 5.12 Visit I – 3rd vaccination

All subjects will receive the third dose with **Comirnaty (BNT162b2)**.

Before IMP injection the following assessment should be performed:

- SARS-CoV-2 PCR Test (not older than 72 hours before vaccination)

- Alternatively: registered antigen test (not older than 24 hours before vaccination), participants will additionally give a sample for a PCR test at visit I prior to vaccination, in case this PCR test is positive the participant will be excluded after vaccination

After IMP injection AEs the subject will be observed for 30 minutes and all AEs/SAEs will be recorded.

Participants should seek immediate medical attention if they develop symptoms such as

- shortness of breath
- chest pain
- leg swelling
- persistent abdominal pain following vaccination
- neurological symptoms including severe or persistent headaches and blurred vision
- skin bruising (petechial) beyond the site of vaccination after a few days

### 5.13 Visit II - VIII (Day 1 – 7 after 3rd vaccination)

Subjects have to report information on reactogenicity between Day 1 and Day 7 after 3rd vaccination. This information will be reported using an eDiary or via telephone call. The following information will be collected:

- pain at injection site
- erythema (redness) at injection site
- swelling/induration (hardness) at injection site
- localized axillary swelling or tenderness ipsilateral to the injection arm
- Headache
- Fatigue
- myalgia (muscle aches all over the body)
- arthralgia (aching in several joints)
- nausea/vomiting
- body temperature (potentially fever)
- chills
- other AEs

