## 5.5 Visit II, IV - VIII (Day 1, 3 – 7 after boost shot)

Subjects have to report information on reactogenicity on Day 1 and between Day 3 and Day 7 after boost shot. This information will be reported using an eDiary or via telephone call. The following information will be collected:

- pain at injection site
- erythema (redness) at injection site
- swelling/induration (hardness) at injection site
- localized axillary swelling or tenderness ipsilateral to the injection arm
- Headache
- Fatigue
- myalgia (muscle aches all over the body)
- arthralgia (aching in several joints)
- nausea/vomiting
- body temperature (potentially fever)
- chills
- other AEs

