**Table 1: Adverse reactions from Comirnaty clinical trials and post-authorisation experience**

| System Organ Class                                   | Very common
(≥ 1/10)                                                             | Common
(≥ 1/100 to < 1/10) | Uncommon
(≥ 1/1,000 to < 1/100)                                                                 | Rare
(≥ 1/10,000 to < 1/1,000)              | Not known
(cannot be estimated from the available data) |
|------------------------------------------------------|-------------------------------------------------------------------------------------|-------------------------------|----------------------------------------------------------------------------------------------------|------------------------------------------------|------------------------------------------------------------|
| Blood and lymphatic system disorders                 |                                                                                     |                               | Lymphadenopathy                                                                                    |                                                |                                                            |
| Immune system disorders                              |                                                                                     |                               | Hypersensitivity reactions (e.g. rash, pruritus, urticaria, a angioedema a ) |                                                | Anaphylaxis                                                |
| Psychiatric disorders                                |                                                                                     |                               | Insomnia                                                                                           |                                                |                                                            |
| Nervous system disorders                             | Headache                                                                            |                               |                                                                                                    | Acute peripheral facial paralysis b |                                                            |

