| Gastrointestinal disorders                           | Diarrhoea c                                                              | Nausea; Vomiting c |                                                                                                    |                                                |                                                            |
| Musculoskeletal and connective tissue disorders      | Arthralgia; Myalgia                                                                 |                               | Pain in extremity d                                                                     |                                                |                                                            |
| General disorders and administration site conditions | Injection site pain; Fatigue; Chills; Pyrexia; e Injection site swelling | Injection site redness        | Malaise; Injection site pruritus                                                                   |                                                |                                                            |

a. The frequency category for urticaria and angioedema was Rare.

b. Through the clinical trial safety follow-up period to 14 November 2020, acute peripheral facial paralysis (or palsy) was reported by four participants in the COVID-19 mRNA Vaccine group. Onset was Day 37 after Dose 1 (participant did not receive Dose 2) and Days 3, 9, and 48 after Dose 2. No cases of acute peripheral facial paralysis (or palsy) were reported in the placebo group.

c. Adverse reaction determined post-authorisation.

d. Refers to vaccinated arm.

e. A higher frequency of pyrexia was observed after the second dose.

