### 7.9.2 Reporting Procedures for SAEs and SUSARs

Investigators be asked to determine for possible AEs. All AEs, whether reported by the patient or noted by study personnel, will be recorded in the patient's medical record and on the Adverse Event eCRF.

**After informed consent** has been obtained but prior to initiation of the study drug, only SAEs considered to be related to a protocol-mandated intervention should be reported (e.g. SAEs related to invasive procedures such as biopsies).

**After initiation of study drug**, all AEs and SAEs regardless of relationship to the study drug will be reported until 7 days or until the event has resolved to baseline grade or better the event is assessed as stable by the investigator the patient is lost to follow-up or the patient withdraws consent.

After 8 days, investigators should report any deaths, SAEs, or other AEs of concern that are believed to be related to prior treatment with the study drug.

Any Serious Adverse Event (SAE) that is ongoing at the time of 7 days should be followed-up until resolved.

In the case of a serious adverse event, the investigator has to use all supportive measures for best patient treatment. The SAE form must be completed by the investigator and reported no more than 24 hours after awareness of the event.

The following details should be available with the initial report:

- patient number
- patient: date of birth, sex
- name of investigator and trial site
- period of administration
- the suspected investigational medicinal product (IMP)
- the adverse event assessed as serious
- concomitant disease and medication
- relevant medical history
- short description of the event and outcome
- description
  - onset and end (if applicable)
  - therapeutic intervention
  - causal relationship to each of the (study drugs)
  - hospitalization or prolongation of hospitalization
  - death, life-threatening, persistent or significant disability or incapacity

If applicable, the initial report should be followed by the follow-up report, indicating the outcome of the SAE.

For SAEs, SUSARs and pregnancies, the sponsor or a designee may follow up by telephone, fax, electronic mail, and/or a monitoring visit to obtain additional case details and outcome information (e.g. from hospital discharge summaries, consultant reports, autopsy reports) in order to perform an independent medical assessment of the reported case. A follow-up SAE form must also be completed and reported appropriately.

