### **Safety Analysis**

Safety evaluations will be based on the incidence, type, severity and consequences (e.g. study discontinuation) of an adverse event (AE) as well as on clinically significant changes in the patient's physical examination, vital signs, and clinical laboratory results (including immunotoxicity). Statistical analysis includes tabulation per treatment group using descriptive measures which are absolute and relative frequencies for categorical data and means, standard deviations, medians and interquartile ranges for continuous data. All safety analyses will be performed on the safety population.

All analyses will be performed in SPSS 26.0 or StataMP 16.0.

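### Diarrhoea is not a named item on the Day 1–7 reactogenicity lists although the protocol's own Comirnaty table rates it very common, so its frequency may be under-ascertained and is not comparable with the prompted symptoms

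*Protocol*

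**What the plan says.** Two sections of the Protocol fix the symptoms collected in the first week.

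- Third dose, section 5.13: "Subjects have to report information on reactogenicity between Day 1 and Day 7", by eDiary or telephone call.
- Boost, section 5.5: "Subjects have to report information on reactogenicity on Day 1 and between Day 3 and Day 7 after boost shot". Day 2 is an on-site visit at which adverse events are recorded (section 5.4).

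The two lists are identical. Each names eleven items and closes with an open line for other adverse events. The only gastrointestinal item is "nausea/vomiting".

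The Comirnaty adverse-reaction table in section 7.1 places diarrhoea in its highest frequency column (at least 1/10), with the footnote "Adverse reaction determined post-authorisation". Nausea and vomiting are one column lower, under common.

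Two further rules matter. Section 7.9.2 requires that "all AEs and SAEs regardless of relationship to the study drug will be reported until 7 days", whether the participant reports them or staff note them. In section 11.3.5, "Safety evaluations will be based on the incidence, type, severity and consequences" of adverse events, tabulated descriptively by treatment group.

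**The concern.** A prompted symptom is asked about by name each time. An unprompted one is recorded only if the participant thinks to mention it or staff draw it out. The lists prompt for the less frequent gastrointestinal reactions to Comirnaty and leave the more frequent one to the open line. The Protocol gives no reason. Section 5.10.3 does name diarrhoea among the symptoms collected from infected participants, so the omission looks like an oversight.

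The gap touches a stated aim. Safety and tolerability after the second dose, and again after the third, are secondary objectives (Synopsis; section 2.2). Every third dose is Comirnaty (section 5.12), and so is every boost given since the homologous Vaxzevria arm closed (sections 5.3 and 6.8). Section 1.4 says that no data on the reactogenicity of a third vaccination are yet available, so the third-dose phase will produce new tolerability data. What is at stake is whether one very common reaction is measured on the same footing as the others in those tables.

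**Working it through.** The Protocol states no figure to reproduce here, and no sample-size, power or error-rate formula applies. The check compares the lists with the table.

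**Step 1. Very common Comirnaty reactions (section 7.1) against the list in 5.13 and 5.5.**

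| Very common after Comirnaty | Named item on the list |
|---|---|
| Headache | yes |
| Arthralgia | yes |
| Myalgia | yes |
| Injection site pain | yes |
| Injection site swelling | yes |
| Fatigue | yes |
| Chills | yes |
| Pyrexia | yes, as body temperature |
| Diarrhoea | no |

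Eight of nine are prompted; diarrhoea is the only one missing.

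**Step 2. Routes by which diarrhoea can still be recorded.**

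- The open line in the same eDiary or call (5.5, 5.13).
- The all-adverse-events rule for the first 7 days (7.9.2).
- On-site visits that record adverse events: Day 2 and Day 10 after the boost (5.4, 5.6), and Day 10 after the third dose (5.14). The third-dose schedule has no Day 2 visit.

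So diarrhoea is collected, but as an unsolicited event.

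**Step 3. What can be said about size.** Let p be the true frequency and c the share of cases that reach the record without a prompt, relative to a prompted question. The expected recorded number per 1000 doses is 1000 × p × c.

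- The table gives only a floor for p: 0.10, hence 1000 × 0.10 = 100 cases per 1000 doses. This assumes that the category applies to these participants and to a third dose.
- The documents give nothing for c. At c = 1 all 100 are recorded and nothing is lost. At any c below 1 the recorded number is 100 × c. The range is open, so no under-count can be computed.

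**Step 4. Comparison between arms.** The list is the same in all arms. If c is also the same, the recorded difference between two arms is c × (p₁ − p₂), and the ratio p₁/p₂ is unchanged. Incomplete capture of that kind would shrink an absolute difference without favouring an arm. Nothing in the documents indicates that c differs by arm.

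**The case against.** The strongest reply is that the Protocol does collect diarrhoea. The open line recurs throughout the diary period and may be taken by telephone. Section 7.9.2 requires every adverse event in the first week, and staff record events at visits. The eDiary form is not shown, so how actively the open line is asked cannot be judged. All of this stands. A reader might infer that diarrhoea will be under-counted, or even that it will appear as 2–5% instead of at least 10%. The second inference needs an assumed capture of 20–50% (100 × 0.2 = 20 to 100 × 0.5 = 50 per 1000). That assumption has no source in the documents, and it excludes higher capture without reason.

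A reader might also take the words on clinical relevance in the section 7.2 definition as an extra filter on mild diarrhoea. They belong to the general definition of an adverse event, and 7.9.2 requires participant-reported events to be recorded, so the point does not rest on them.

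It is also fair to say that the Protocol never promises to prompt for every very common reaction. Its Vaxzevria table lists injection site warmth, pruritus and bruising, and malaise, as very common, and none is a named item. The safety endpoint is the occurrence of adverse events, diarrhoea is not an adverse event of special interest, and the analysis is descriptive. This limits the weight of the point. It does not remove it, because every dose still to be given is Comirnaty and diarrhoea is the single gap against that product's very common reactions.

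**Conclusion.** The point holds in a limited form. Diarrhoea is not prompted although the Protocol's Comirnaty table rates it very common, above the prompted nausea and vomiting. It reaches the record only as an unsolicited event. Its frequency may therefore be under-ascertained, and it is not directly comparable with the eight very common reactions that are prompted.

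The only size that follows from the documents is the floor of about 100 expected cases per 1000 Comirnaty doses, on the assumption that the table's category carries over to this population and to the third dose. How many of those would be missed, if any, cannot be derived. No bias between arms is shown. The primary endpoint, the sample size and the planned tests are unaffected. It is a modest point, worth acting on because the correction is one diary item and prompted data cannot be recovered afterwards for doses already given.

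**What to change.** Add diarrhoea as a named item in section 5.13 and, for participants still to be boosted, in section 5.5. In the safety tables, show it as solicited only for doses given after the change and as unsolicited for earlier doses, with the collection method stated in the table.

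The direct cost is one more eDiary or telephone question. The real downside is a change of method during the study. Section 1.3 reports about 300 participants already recruited under the present list. Many could have diarrhoea unprompted after the second dose and prompted after the third, and an apparent rise could then come from the prompting alone. Section 11.3.3 plans a before-and-after comparison of the second and third doses for efficacy, so a reader may try the same for tolerability. The report should state that diarrhoea rates after the two doses are not to be compared where the collection method differs.

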### 5.14 Visit IX (Day 10 ± 1 day after 3rd vaccination)

The following assessments will be performed on Visit IX:

- Physical examination including vital signs
- Blood draw
  - Coagulation (PT INR, antithrombin III, fibrinogen, D-Dimer, APTT)
  - CRP
  - Blood chemistry (albumin, alkaline phosphatase, aspartate aminotransferase (AST), alanine aminotransferase (ALT), lactate dehydrogenase (LDH), Gamma-GT, creatinine, uric acid, total bilirubin, total protein, blood urea nitrogen)
- Hematology (Hematocrit, Hemoglobin, platelet count, WBC, RBC)
- AEs/SAEs
- Immunogenicity blood draw:
  - 9 ml EDTA for antibody testing
  - Up to 45 ml EDTA/heparin for T-cell analysis

### 5.15 Visit VIII, X – XXXIII (every 7 days ± 2 day after 3rd vaccination)

Every 7 days (± 2) after 3rd vaccination until Day 182 subjects have to undergo antigen or RT-PCR testing. If this test confirms an infection with SARS-CoV-2, the clinical course and outcome will be followed. Virus from swabs will be isolated and sequenced and further analyzed for immune escape.

In addition, subjects complete their reports in the eDiary or via telephone call.

### 5.16 Additional visits on Day 30 (AV 1), Day 90 (AV 2) and Day 180 (AV 3) after 3rd vaccination (± 3 day)

The following examinations will be performed:

- Physical examination including vital signs
- Blood draw:
  - 9 ml EDTA for antibody testing
  - Up to 45 ml EDTA/heparin for T-cell analysis
- Concomitant medication
- Concomitant vaccination

- AEs/SAEs

### 5.17 Unscheduled Visits after 3rd vaccination

Unscheduled visits will not be integrated in the study except when they are related to a positive SARS-CoV-2 RT-PCR result or an adverse event.

### 5.18 Study Assessments after 3rd vaccination

See study assessments after boost vaccination above. The following derivations to the procedures described above are applied after the 3rd vaccination: no lab values on day 2 and 10; all participants will be analyzed for T cell responses on day 10, 30, 90 and 180.

### 5.19 Discontinuation of the Study/Premature Termination of the Trial

The sponsor has the right to discontinue a participating site in this trial at any time. Reasons for discontinuing site participation may include, but are not limited to the following:

- patient enrolment is unsatisfactory
- administrative reasons

The sponsor will notify the investigator if the sponsor decides to discontinue the participation of the site.

The sponsor has the right to terminate the trial prematurely at any time, due to any relevant medical or ethical concerns. The reasons for terminating the trial must be documented in detail. All trial subjects still under treatment at the time of termination must undergo a final examination which must be documented. The principal coordinating investigator must be informed without delay if any investigator has ethical concerns about continuation of the trial.

Premature termination of the trial will be considered if:

- the risk-benefit balance for the trial subjects changes markedly
- it is no longer ethical to continue treatment with the IMP
- the sponsor considers that the trial must be discontinued for safety reasons (e.g. advice of the DSMB)
- An interim analysis or results of other research show that one of the trial treatments is superior or inferior to another
- it is no longer practicable to complete the trial

The sponsor decides about discontinuation of the trial in consultation with the PCI, DMC and/or statistician.

In case of discontinuation of the trial the IEC and competent regulatory authority must be informed within 15 days about early termination.

## 5.20 Closure of the Study

The clinical trial ends when the last subject has completed the planned last visit according to protocol.

The completion of the study will be reported to the ethics committee as well as to the relevant authorities.

## 6. Study Medication (IMP)

### 6.1 Vaxzevria Suspension for injection and Comirnaty concentrate for dispersion for injection

Vaxzevria is a chimpanzee adenovirus encoding the SARS-CoV-2 Spike glycoprotein (ChAdOx1-S) and is produced in genetically modified human embryonic kidney (HEK) 293 cells by recombinant DNA technology. Vaxzevria is indicated for active immunization to prevent COVID-19 caused by SARS-CoV-2, in individuals 18 years of age or older.

Comirnaty is a single-stranded, 5'-capped messenger RNA (mRNA) produced using a cell-free in vitro transcription from the corresponding DNA templates encoding the viral spike (S) protein of SARS-CoV-2. Comirnaty is indicated for active immunization to prevent COVID-19 caused by SARS-CoV-2 virus, in individuals 16 years of age and older.

